### Outcome measurements

#### Primary outcome

The primary outcome is the change in eGFR over 12 months. Decline of eGFR has been widely applied as primary outcome in several trials, such as the Hypertension (AASK) [20], MDRD Study [21] and the Ramipril in Non-diabetic Renal Failure Study (REIN) [22]. The eGFR will be calculated by the CKD-EPI (Chronic Kidney Disease Epidemiology Collaboration) formula [23], and evaluated at baseline, and after 3, 6, 9 and 12 months of the follow-up period.

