### Sample size calculation

The sample size calculation will be based upon a retrospective analysis of the change in eGFR in patients with stage 4 CKD treated at our hospital between 2003 to 2010, and Hou’s trial published in 2006 [12]. Our retrospective analysis indicated that the mean eGFR decrease was 4.5 ± 4.2 ml/min/1.73 m^2^ per year in patients with stage 4 CKD treated with CM. Hou’s trial reported that the median rate of GFR decrease was around 6.8 ml/min/1.73 m^2^ per year in patients with stage 4 CKD receiving benazepril [12]. PASS 2008 software (NCSS, LLC, Kaysville, Utah, USA) was used to calculate the sample size required for the current study to allow a superiority test to be performed for the BYF group versus the losartan group where 1 ml/min/1.73 m^2^ GFR is considered to indicate a clinically important difference with a 90 % power and a one-tailed significance level of 2.5 %. The study was calculated to require 221 patients per group. Predicting a 20 % lost to follow-up rate, we adjusted the total sample size to 277 for each group.

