### Statistical analyses

An independent team of data managers and statisticians from KUMCR, will be responsible for the data management and statistical analysis of this study. The statisticians will be blinded to the randomized allocation of groups. PAWS 18.0 (IBM SPSS Inc., Armonk, New York, USA) and SAS 9.2 (SAS Institute Inc., Cary, USA) statistical software packages will be used to analyze the data.

Prior to analyses, the statistical analysis plan will be written, updated and confirmed after blind data review. The full analysis population is defined as patients randomized to receive at least one treatment dose, with baseline and at least one post-baseline efficacy assessment. The per-protocol population is defined as patients who complete the course of the study without a major protocol violation. The primary outcome analysis is based on full analysis population, intention-to-treat principle and the per protocol population. An intention-to-treat analysis will be applied using the imputation method for missing data. The linear trend at point method will be used to replace missing values. The existing series will be regressed on an index variable scaled 1 to n, and the missing values will be replaced with their predicted values. If the predicted values cannot be computed, the last observation carried forward (LOCF) method will be used for this variable. For analysis of endpoint events, a mixed effect model will also be employed, adjusting for co-variables including baseline characteristics. After reporting descriptive statistics of baseline characteristics for each group, an effectiveness analysis will compare the BYF and losartan groups, and a superiority test, with a 95 % confidence interval for eGFR, will be performed to investigate the clinical difference associated with BYF.

The eGFR will be analyzed using a mixed effect GLM with terms for treatment, time point, center, and some baseline characteristics as co-variables based on the concept of repeated measure analysis or adjusted nominal significance level. The Mann–Whitney U-test will be used to analyze ordinal categorical variables. An analysis of variance (ANOVA) will be used for numerical variables, and a Chi-square test or Fisher exact test will be used for categorical variables.

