An analysis of covariance will be used for continuous variables, and the Cochran–Mantel–Haenszel test will be used for categorical variables to adjust for the center effect. Unconditional logistic regression analysis will be used for the curative effect factors analysis. The Kaplan–Meier method will be used to assess the incidence and mean occurrence time of endpoint events. Cox proportional hazards regression will be used to analyze factors influencing the incidence of endpoint events. Subgroup analysis of risk factors including hypertension, proteinuria will be performed. The Fisher exact test will be used to compare the incidence rates of AEs and adverse drug reactions over the course of treatment.

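### The eGFR mixed model, as listed, estimates an average over visits, while the endpoint and sample size concern the 12-month change

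*Protocol article*

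**What the plan says.** All references are to the protocol article.

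- **Primary outcome:** "The primary outcome is the change in eGFR over 12 months". eGFR is "evaluated at baseline, and after 3, 6, 9 and 12 months of the follow-up period".
- **Sample size calculation:** for the Chinese medicine arm, "the mean eGFR decrease was 4.5 ± 4.2 ml/min/1.73 m^2^ per year in patients with stage 4 CKD treated with CM". The comparator figure is a decline of about 6.8 per year (a median, under benazepril). A difference of 1 ml/min/1.73 m² is called clinically important. Power is 90% at one-sided 2.5%, giving 221 per group, or 277 after 20% loss to follow-up.
- **Statistical analyses, eGFR model:** a "mixed effect GLM with terms for treatment, time point, center, and some baseline characteristics as co-variables", described as "based on the concept of repeated measure analysis or adjusted nominal significance level".
- **Statistical analyses, superiority:** "a superiority test, with a 95 % confidence interval for eGFR, will be performed to investigate the clinical difference associated with BYF". No visit, model term or margin is named.
- **Statistical analyses, other numerical outcomes:** "An analysis of variance (ANOVA) will be used for numerical variables". A later paragraph adds: "An analysis of covariance will be used for continuous variables". That sentence ends with adjustment for centre.

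**The concern.** In a repeated-measures model with a treatment term and a time term but no interaction, the treatment coefficient is one arm difference shared by all visits. It equals the 12-month difference only if the arms separate fully by the first modelled visit and then stay parallel. The trial's own hypothesis is different: the Background and Discussion speak of slowing progression, and the sample size states the effect as annual rates of decline. A slowed decline produces a gap that grows with time, so a visit-average is smaller than the gap at month 12.

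Two things are at stake. The reported effect could understate the 12-month benefit. And if the visit-average is tested against the margin of 1 that underlies the sample size, most of the planned power could be lost. The wording also leaves two routes open for the primary analysis, repeated measures or a significance-level adjustment, so a reader cannot tell which one decides the trial.

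A smaller matter concerns the secondary numerical outcomes. They are measured at baseline, yet plain ANOVA is named for them, which leaves available precision unused.

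**Working it through.** **1. The plan's own figure.** Inputs from Sample size calculation: declines 4.5 and 6.8, SD 4.2, difference of importance 1, one-sided alpha 2.5%, power 90%.

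- Difference: 6.8 − 4.5 = 2.3. Net of a margin of 1: 1.3.
- Normal approximation: n = 2 × (1.960 + 1.282)² × 4.2² / 1.3² ≈ 219.4, so 220 per group. With the noncentral t, n = 220 gives 89.96% and n = 221 gives 90.09%, so **221** reproduces.
- Dropout: 221 / 0.8 = 276.25, so **277**.
- Other readings fail: a difference of 1.0 needs 371 per group, and 2.3 against zero needs 71.

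The powered test is therefore the one-year difference against a margin of 1.

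**2. What the listed terms estimate.** Assume that the arms diverge linearly from zero at baseline and that visits get equal weight.

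- Months 3, 6, 9, 12 as responses: (3 + 6 + 9 + 12) / (4 × 12) = 0.625. Then 2.3 × 0.625 = 1.4375.
- Baseline also a response: (0 + 3 + 6 + 9 + 12) / (5 × 12) = 0.50. Then 2.3 × 0.50 = 1.15.

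**3. Power at 221 per group.** Power = Φ(d / (SD × √(2/221)) − 1.96), where d is the difference net of the margin. The SD of a visit-average is not in the documents, so a range is shown. Post-baseline visits only:

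| Assumed SD of the average | Against margin 1 (d = 1.4375 − 1 = 0.4375) | Against 0 (d = 1.4375) |
|---|---|---|
| 4.2 | 19% | 95% |
| 3.0 | 33% | >99% |
| 2.625 | 42% | >99% |
| 2.1 | 59% | >99% |

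Worked line for SD 4.2: SE = 4.2 × √(2/221) = 0.400; 0.4375 / 0.400 − 1.96 ≈ −0.87; Φ ≈ 0.19.

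To keep 90% against the margin, the SD would have to be 0.4375 / (√(2/221) × 3.2415) ≈ 1.42. With baseline as a response, d = 0.15 and power against the margin is about 6% (SD 4.2) to 11% (SD 2.1).

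**4. With the month-12 contrast.** A treatment-by-visit term and the month-12 difference return the design figures: net 1.3, SD 4.2, 221 per group, 90%.

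**5. Secondary outcomes.** With baseline correlation ρ and equal variances, the variance of baseline ANCOVA relative to a comparison of change scores is (1 + ρ)/2. That is a saving of 25% at ρ = 0.5 and 10% at ρ = 0.8. Relative to a comparison of final values it is 1 − ρ², a saving of 25% and 64%. These values of ρ are assumptions.

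**The case against.** The strongest reply is that a journal article condenses the plan. It nowhere says that the listed terms are complete. A group-by-time term is routine in repeated-measures work, and the article says that an analysis plan will be written before analysis. It also names a separate superiority test and an ANCOVA for continuous variables, either of which could be applied to the 12-month change.

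Much of this stands. A reader might infer that the plan cannot deliver the powered test. The documents do not support that, because the superiority test is not tied to the model's treatment coefficient and may turn out to be a month-12 comparison. What remains is that the article does enumerate the terms of the eGFR model, and followed as written they do not give the quantity that was defined and powered. Neither the superiority sentence nor the ANCOVA sentence names month 12, so neither closes the gap.

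A reader might also take 62.5%, or any one power figure, as a property of the trial. It is not. It rests on linear divergence and equal weights. Full separation by month 3 would give 100%, and unequal weights under another covariance structure would change the share. The power loss further requires the final test to use the margin of 1, which the analysis section does not state.

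Finally, a reader might see result-driven choice in covariates that are not yet fixed. The article says that the data review is blind and precedes analysis, and that the statisticians are blinded to allocation. That answers the worry.

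On the secondary outcomes, ANOVA is a valid randomised comparison, and the ANCOVA sentence may be meant to cover baseline values.

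**Conclusion.** The point holds as a mismatch between a stated model and its endpoint. As listed, the eGFR model yields an effect averaged over visits; the primary outcome and the 221 per group concern the 12-month difference with a margin of 1.

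The size is conditional. Under linear divergence and equal weights, the estimate would be about 37.5% below the 12-month difference, or 50% below if baseline is a response. With post-baseline visits only, power against the margin would drop from 90% to somewhere between 19% and 59% for the assumed SDs, and power against zero would remain about 95% or more. The direction follows from the trial's own hypothesis of slowed progression; the exact figures do not come from the documents.

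Because the mismatch affects the primary conclusion, it should be settled before unblinding. The secondary-outcome point is a gain in precision, not the correction of an error.

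**What to change.** - State one primary model for eGFR: treatment, visit, treatment-by-visit, baseline eGFR and centre.
- Name the treatment difference at month 12, with its 95% CI, as the primary superiority test. State that it is tested against the margin used in the sample size.
- Delete the alternative of a significance-level adjustment from the model sentence, so that a single route remains.
- For secondary numerical outcomes with a baseline value, replace plain ANOVA with ANCOVA on that baseline and centre.

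The cost is wording in the protocol and the analysis plan. Baseline and all follow-up eGFR values are already scheduled, and the sample size does not change.

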**Table 1 Tab1:**
[figure not shown]
Schedule of study

The urinary protein creatinine ratio will be examined at baseline, and at 3, 6, 9 and 12 months. Serum creatinine level (SCr) and blood urea nitrogen level (BUN) will be measured at baseline, and at 1, 2, 3, 6, 9, and 12 months. Biochemical tests including plasma albumin, triglyceride, cholesterol, calcium, phosphate, and intact parathyroid hormone level (iPTH) will be measured at baseline, and at 3, 6, 9, and 12 months.

We will assess the patient's cardiovascular function by left ventricular ejection fraction (LVEF), interventricular septal thickness (IVST), left ventricular posterior wall thickness (LVPWT), carotid artery intima-media thickness (CIMT) through the Carotid Doppler and Cardiac Doppler, which will be measured at baseline and 12 months.

The Kidney Disease Quality of Life Instrument (KDQOLSF 1.3) scale will be evaluated at baseline and at 6 and 12 months.

Endpoint events are defined as serum creatinine level increasing to double the baseline level, ESRD (requiring permanent dialysis or kidney transplantation), cardiovascular or cerebrovascular events (acute myocardial infarction, heart failure, ischemic cerebral infarction or cerebral hemorrhage verified by typical clinical manifestations, electrocardiogram (ECG) alterations, and imaging and laboratory investigations) or death. The nature and severity of events will be recorded as endpoint events during the follow-up period.

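### Numerical secondary outcomes get ANOVA or ANCOVA with no stated term for their own baseline and no repeated-measures model, which gives up precision the collected data could supply

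*Protocol article*

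**What the plan says.** The Statistical analyses section assigns methods by type of variable. For numerical variables in general: "An analysis of variance (ANOVA) will be used for numerical variables". The next paragraph adds a second method for what appears to be the same class of variable: "An analysis of covariance will be used for continuous variables, and the Cochran–Mantel–Haenszel test", and the sentence continues "will be used for categorical variables to adjust for the center effect". No covariate is named there, and centre is the only purpose given.

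One numerical outcome is treated differently: "The eGFR will be analyzed using a mixed effect GLM with terms for treatment, time point, center, and some baseline characteristics as co-variables". That model is described as resting on repeated-measures thinking.

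The Secondary outcomes section sets the measurement times:

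- LVEF, IVST, LVPWT and CIMT, "which will be measured at baseline and 12 months": one follow-up visit.
- KDQOL: "The Kidney Disease Quality of Life Instrument (KDQOLSF 1.3) scale will be evaluated at baseline and at 6 and 12 months", so two follow-up visits.
- Protein-creatinine ratio: "The urinary protein creatinine ratio will be examined at baseline, and at 3, 6, 9 and 12 months", so four. Albumin, lipids, calcium, phosphate and iPTH also have four.
- Serum creatinine and BUN: baseline and six later visits.

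**The concern.** Every one of these outcomes has a baseline value for the same patient, and most have several later values. Read literally, neither the ANOVA sentence nor the ANCOVA sentence uses the baseline value, and neither says how repeated visits enter. An ANOVA of follow-up values leaves in the error term between-patient variation that the baseline could remove, and it lets chance baseline imbalance pass into the estimated treatment difference.

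The contrast with eGFR is sharpest for serum creatinine. The Quality control section says eGFR is estimated from serum creatinine. Yet eGFR, with four follow-up visits, gets a repeated-measures model, while creatinine, with six, falls under the generic sentence. At stake is precision on secondary outcomes, including quality of life, on which the Conclusions section says BYF will be assessed.

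**Working it through.** **The plan's own figure.** The article gives no power or sample size for any secondary outcome. Its only calculation is for the primary outcome, and it reproduces. The difference beyond the margin is 6.8 − 4.5 − 1 = 1.3, with SD 4.2, one-sided 2.5% and 90% power. Then 2 × (1.96 + 1.2816)² × 4.2² / 1.3² gives 220 per group by the normal approximation and 221 with the t distribution, as stated. Dividing, 221 / 0.80 = 276.25, rounded up to 277. The present point does not touch this.

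**Inputs for the check.** The documents give no correlation ρ between baseline and follow-up. I assume ρ = 0.5 with a range of 0.3 to 0.7, and equal variance at both times.

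**Variance of the treatment difference, relative to ANOVA of the follow-up value (= 1):**

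- ANOVA of change from baseline: 2(1 − ρ)
- ANCOVA with baseline as covariate: 1 − ρ²

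| ρ | Follow-up ANOVA | Change ANOVA | Baseline ANCOVA | Cut vs follow-up | Cut vs change, 1 − (1 + ρ)/2 |
|---|---|---|---|---|---|
| 0.3 | 1 | 1.40 | 0.91 | 9% | 35% |
| 0.5 | 1 | 1.00 | 0.75 | 25% | 25% |
| 0.7 | 1 | 0.60 | 0.51 | 49% | 15% |
| 0.8 | 1 | 0.40 | 0.36 | 64% | 10% |
| 0.9 | 1 | 0.20 | 0.19 | 81% | 5% |

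For ρ = 0.7 the entry of 49% is 1 − 0.51; the residual variance that remains is 51%.

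**In terms of power.** Take, for illustration, a contrast with 80% power at two-sided 5%, so that the noncentrality is 1.96 + 0.84 = 2.80.

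- From follow-up ANOVA to ANCOVA, divide by √(1 − ρ²). At ρ = 0.5, 2.80 / 0.866 = 3.24, and Φ(3.24 − 1.96) gives 90%. At 0.3 it is 84% and at 0.7 it is 98%.
- From change-score ANOVA to ANCOVA, multiply by √(2 / (1 + ρ)). Power becomes 94%, 90% and 86% at ρ = 0.3, 0.5 and 0.7.

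**In terms of patients.** The precision that 221 per group give under follow-up ANOVA would be reached under ANCOVA with 221 × 0.75 = 166 per group at ρ = 0.5 (202 at 0.3, 113 at 0.7).

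I put no figure on any further gain from modelling several visits jointly, because that depends on correlations between visits that the documents do not give.

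**The case against.** The ANOVA sentence is one entry in a list of methods by variable type. It does not say whether the response is a raw value or a change, or whether ANOVA is run per visit, at month 12 only, or in repeated-measures form. ANOVA of change would use the pairing with baseline, and repeated-measures ANOVA would use the within-patient correlation. In the ANCOVA sentence, the centre phrase may belong to the Cochran–Mantel–Haenszel test alone. An analysis of covariance normally carries a continuous covariate, and the baseline value is the obvious one. A condensed article can also leave such detail to the analysis plan that it says will be written.

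Much of this stands. The text does not rule out use of the baseline, so it cannot be said that the plan ignores it, only that no such use is stated. It is also true that ANOVA at a single visit in a randomised trial is valid.

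A reader might go further and infer that the several visits would enter one ANOVA as independent observations, so that false positives exceed 5%. The article does not support that. It nowhere describes pooling, its eGFR model shows awareness of repeated measurement, separate tests at each visit keep their nominal level apart from multiplicity, and the cardiac and carotid measures have only one follow-up.

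The objection does not remove the suggestion itself. The article states a method rather than leaving one open, two methods overlap without a rule for choosing between them, and a better one is already planned for eGFR in the same section.

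**Conclusion.** The point holds as an inexpensive improvement to the secondary analyses, not as an error that invalidates them. If ANOVA is applied to follow-up values as written, the comparisons are valid but lose precision. Baseline adjustment would reduce residual variance by about 25% at an assumed correlation of 0.5. The reduction is 9% at 0.3, and at 0.7 the factor 1 − ρ² is 0.51, so the reduction is about half (49%). If the intention is ANOVA of change scores, the advantage of ANCOVA falls from 35% at 0.3 to 15% at 0.7 and only 5% at 0.9. All these figures rest on assumed correlations, and the powers also rest on an assumed starting value of 80%. The primary analysis and the 221 and 277 per group are unaffected, and there is no basis in the document for a claim about false positives.

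**What to change.** Replace the generic ANOVA and ANCOVA wording for numerical secondary outcomes with two statements.

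1. LVEF, IVST, LVPWT and CIMT: ANCOVA of the 12-month value on treatment, the outcome's baseline value and centre.
2. KDQOL, serum creatinine, BUN, the biochemical tests and the protein-creatinine ratio: the mixed repeated-measures model already planned for eGFR, with the outcome's own baseline value, centre, visit, treatment and treatment-by-visit, reporting the between-group contrast at 12 months.

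The cost is wording in the analysis plan, settled before unblinding. The baseline values are already scheduled and SAS is already named. A short rule is needed for patients who lack the baseline value of a particular outcome.

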### Intervention

Enrollment will be followed by a 3-week run-in period, and then patients will receive BYF plus losartan-matched placebo (CM group) or losartan plus BYF-matched placebo (losartan group) for one year. Patients with unstable BP within the six weeks prior to enrollment that are taking ACEi/ARBs, will be administered other types of antihypertensive agents to reduce BP below 140/90 mmHg.

All Chinese herbs will be obtained from Guangdong Kangmei Pharmaceutical Co. (Guangzhou, Guangdong, China). All herbs will be authenticated by macroscopic and microscopic examination of cross sections, chemical tests and chromatographic analysis. To ensure these herbs are safe for human consumption the agricultural residue screening test for heavy metals, pesticides, and aflatoxins will be performed.

The BYF herbs will be extracted with hot water, then concentrated, spray-dried, and packed in sealed opaque sachets. The entire manufacturing process will comply with Chinese GMP. Sandoz Corp. Ltd. (Zhongshan city, Guangdong, China) will produce the losartan tablet placebos with an identical appearance, smell and taste, packed in exactly the same way.

In the BYF group, patients will be instructed to dissolve a BYF sachet in 150 ml of boiled water and to take this solution orally three times daily and a losartan-matched placebo daily for 1 year. Patients in the losartan group will be instructed to take 100 mg losartan orally once daily and also a placebo sachet dissolved in 150 ml of boiled water three times daily for 1 year.

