**Chart 1 Fig4:**
[figure not shown]
Underlying Multi-compound, multi-target, multi-pathway network of Bupi Yishen formula in retarding progression of chronic kidney disease

**Table 2 Tab2:** Buipi Yishen formula

Herb	Ratio
*Astragalus mongholicus*	6
*Codono psispilosula*	4
*Macrocephalae*	3
*Poria cocos*	3
*Rhizoma dioscoreae*	3
*Semen Cuscutae*	3
*Radix Polygoni Multiflor*	3
*Semen coici*	4
*Salvia miltiorrhiza*	3

The chemical content of BYF was assessed by Ultra-performance liquid chromatography-mass spectrometry (LC-MS), and the five major chemical components were found to be Salvianolic acid B, Calycosin, Cuscutic acid C, glycerin trioleate and Astragaloside I (Figs. 2 and 3). In 2014, the BYF formula and the methods of producing it were approved and patented as a treatment for CKD by the Chinese State Intellectual Property Office (NO. 2012100298628).

In this trial, the efficacy of BYF will be compared to losartan. In CKD, patients’ GFR diminishes, and the risk of cardiovascular disease increases. ACEI/ARBs are known to exert both renal and cardiac protective effects. Recently, the ROAD study confirmed the benefit of ARB in stage 4 CKD [8]. Therefore, it is appropriate to choose losartan as a positive control rather than placebo. Though Losartan may improve outcomes of CKD patients, more efficacious treatments would still be desirable. Based on the concern above, this study has been designed to compare the effect of CM with the effects of losartan.

The conclusions that may be drawn from the results of this trial are limited by the lack of long-term follow-up and evaluation. However, when the trial ends, those patients that have not reached the endpoints will be admitted to our research-based clinic and continue the optimized CM treatment. All patients will be followed up until they reach the endpoint. Further findings of this trial will be updated.

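### The Kaplan-Meier mean time to an endpoint event is not identified with 12 months of randomized follow-up and no stated horizon

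*Protocol article*

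**What the plan says.** In the protocol article, Statistical analyses, the Kaplan-Meier method "will be used to assess the incidence and mean occurrence time of endpoint events". No truncation time is attached to the mean. The events are doubling of serum creatinine, ESRD, cardiovascular or cerebrovascular events, and death (Secondary outcomes).

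Three places fix the time frame. Under Intervention, the arms are treated for a year; the control arm, for example, takes "losartan plus BYF-matched placebo (losartan group) for one year". Under Primary outcome, eGFR is "evaluated at baseline, and after 3, 6, 9 and 12 months of the follow-up period". Under Secondary outcomes, "The nature and severity of events will be recorded as endpoint events during the follow-up period".

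The Discussion says that the conclusions are "limited by the lack of long-term follow-up and evaluation". It foresees patients without an endpoint when the trial ends. They are to move to the organizers' clinic for further Chinese medicine treatment, and all patients are to be followed until an endpoint occurs.

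Two other methods are named for these events: "Cox proportional hazards regression will be used to analyze factors influencing the incidence of endpoint events", and "For analysis of endpoint events, a mixed effect model will also be employed", adjusted for covariates.

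**The concern.** A mean time to event is the whole area under the survival curve, so it can be estimated only if the curve falls to zero within the observed time. Here observation under randomized treatment lasts 12 months, and the article itself foresees event-free patients at that point. The part of the curve that determines most of the mean is never seen.

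Software will still print a number: the area up to some cut-off. If the cut-off is specific to each arm, such as that arm's last observation or last event, the two areas cover different lengths of time. Their difference can then be shifted or made noisier for reasons unrelated to treatment. A reader of the results could take such a figure for a delay of events.

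**Working it through.** **The plan's own figures.** The article states no event rate and no figure for the mean time. Its one planning figure is for eGFR and reproduces. The difference is 6.8 − 4.5 − 1 = 1.3, with SD 4.2, one-sided 2.5% and 90% power. The t-based calculation gives 221 per group, and 221/0.8 = 276.25, rounded up to 277. It is used below only for the size of the simulated arms.

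**Inputs.** Horizon 12 months, 277 per arm and 20% dropout come from the article. The 12-month event rate p is an assumption, shown from 10% to 40%.

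**Is the event rate likely to be far below 100%?** A rough check takes creatinine doubling as at least a halving of eGFR. It treats the annual decline as normal with the article's means (4.5 for Chinese medicine, 6.8 for control) and applies its SD of 4.2 to both arms. The chance is 1 − Φ((b/2 − m)/4.2) for baseline b and mean decline m.

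- b = 22.45 (mid-range for stage 4): 5% and 15%.
- b = 15 (lowest eligible): 24% and 43%.

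This covers only the creatinine component, but it shows that the curve will not approach zero in a year.

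**Formulas.** With constant hazard, λ = −ln(1 − p)/12. The unrestricted mean is 1/λ, and the area to T is R(T) = (1 − e^(−λT))/λ. If the hazard is multiplied by k after month 12, the mean is R(12) + (1 − p)/(kλ).

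Example, p = 20%: λ = 0.2231/12 = 0.0186, so 1/λ = 53.8 and R(12) = 0.20/0.0186 = 10.76 months.

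| Assumed 12-month event rate | 10% | 20% | 30% | 40% |
|---|---|---|---|---|
| Unrestricted mean (months) | 113.9 | 53.8 | 33.6 | 23.5 |
| Same, hazard halved after month 12 | 216.4 | 96.8 | 57.2 | 37.6 |
| Same, hazard doubled after month 12 | 62.6 | 32.3 | 21.9 | 16.4 |
| Area to 12 months | 11.39 | 10.76 | 10.09 | 9.40 |
| Added if one arm is cut at 12.5 months | 0.45 | 0.40 | 0.35 | 0.30 |
| Added if one arm is cut at 13 months | 0.90 | 0.79 | 0.69 | 0.59 |
| Change in area to 12 months, hazard ratio 0.75 | 0.15 | 0.29 | 0.44 | 0.57 |

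The first three rows show that the unseen tail decides the mean. The last three set an artefact of the cut-off against a real effect. A half-month gap exceeds the effect at 10% and 20%, but not at 30% or 40%. A one-month gap exceeds it throughout, though only just at 40%.

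**Simulation.** Both arms had the same hazard, 277 patients, 20% dropout and final visits within a quarter month of month 12, over 1,000 runs. The arm difference in the Kaplan-Meier mean was:

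- Each arm cut at its own last observation, equal visit windows: average about 0.00 month at 10% and at 30%.
- Same rule, one patient in one arm seen one month beyond the window: 0.90 month at 10% and 0.71 at 30%. Two months beyond: 1.80 and 1.41.
- Each arm cut at its own last event, equal windows: no systematic shift, but an SD of 0.74 month at 10%, against 0.18 with a common cut-off.
- One common cut-off (11.5 months): average between 0.00 and 0.01 month in every setting.

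**The case against.** The strongest defence is that the mean is not what the trial promises. The Abstract and Conclusions speak of the incidence of endpoint events. Kaplan-Meier incidence at 12 months is estimable and stands in the same sentence. This is right, and it limits the point to one quantity.

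A reader might infer that no valid treatment comparison of endpoint events is planned, because no log-rank test is named, Cox regression is tied to influencing factors and a mixed model is added. The article does not support that. Chi-square or Fisher tests are planned for categorical variables, with a Cochran-Mantel-Haenszel test to adjust for center, and both can compare event incidence. Treatment is not excluded from the Cox factors. The mixed model has a stated role, covariate adjustment. A log-rank test can be left to the separate analysis plan that the article announces.

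A reader might also infer that the reported mean will be biased by more than any real effect. That is not supported either. The article names two software packages and no cut-off rule. Follow-up is of fixed length, randomization is stratified by center and the trial is blinded, so unequal last observations are a possibility, not an expectation. With equal visit windows the shift averages about zero.

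Finally, the Discussion's follow-up of all patients until an endpoint might seem to supply the missing tail. It begins after the trial, and patients without an endpoint then move to Chinese medicine treatment. It gives no randomized comparison of time to event.

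It can be argued that the horizon of a restricted mean is itself a detail for the analysis plan. But the article is not merely silent: it names a mean, which this follow-up cannot deliver.

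**Conclusion.** The point holds in a limited form. The stated mean is not identified. That needs only the 12-month horizon and some patients still event-free, and both are in the article. The illustrative sizes are about 114 to 24 months for the unrestricted mean, and 0.30 to 0.45 month of artefact per half-month gap, against 0.15 to 0.57 month for a hazard ratio of 0.75. They rest on assumed event rates of 10% to 40% and a constant hazard. The artefact also requires a cut-off at each arm's last observation and last observations that differ between arms. A cut-off at each arm's last event adds noise, not systematic shift. Severity is minor: this is one summary of a secondary outcome, and neither the incidence analysis nor the primary outcome is touched.

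**What to change.** In Statistical analyses, make one of two changes:

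- Replace the mean with the restricted mean event-free time to one horizon common to both arms: 12 months, or the latest time at or before it that both arms reach.
- Drop the mean and report the 12-month Kaplan-Meier cumulative incidence per arm, with the difference and its 95% confidence interval.

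A median is no substitute, because it would not be reached at any event rate in the assumed range. State also that events after the end of the randomized year do not enter the randomized comparison. The cost is a change of wording: no new data, visits or patients.
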